### Primary outcomes

2.9

The ISI scores for the severity of CI before and the 10th day of treatment, 30th day of follow-up. The RMT for excitability of the motor cortex before and the 10th day of treatment, 30th day of follow-up.

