### Study group

2.5

Forty-five participants who meet the criteria with informed consents will be selected. The subjects will be randomly divided into 3 groups in a 1:1:1 ratio, namely the experimental group, positive-control group and waiting list control group, 15 cases in each group.

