### Estimation of sample size

2.11

This study is just a pilot study, which designed for efficacy evaluation and mechanism investigation of targeted therapy preliminarily before and after treatment as well as follow-up period. We will plan to enroll a total of 45 participants in this study.

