### Statistical analysis

2.13

Data analysis will be based on intention-to-treat analysis and/or per-protocol analysis principle in the light of data missingness. We will also evaluate the group effect by comparing the analysis results between the above 2 data sets to evaluate robustness of our analytical results.

All data will be analyzed using SPSS23.0 (v23.0; SPSS Inc, Chicago, IL) by 3rd-party statistician. A *P* value <.05 will be considered as significant. Descriptive statistics will be performed with mean, standard deviation, maximum, minimum, and so on by groups and time.

Baseline characteristics of patients will be summarized by groups and compared with Chi-squared for categorical variables, and analysis of variance (ANOVA) (normal distributions) or Kruskal–Wallis test (non-normal distributions) for the continuous variables. Primary and secondary outcomes according to the measurement times are applicable to univariate repetitive measurement deviation analysis or ANOVA or Kruskal–Wallis test. If there is a violation of distribution assumption, appropriate transformation will be used.

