#### Primary outcomes

2.13.1

We will use univariate repetitive measurement deviation analysis with ISI scores and RMT before and the 10th day of treatment, 30th day of follow-up as the outcomes. A significant effect of group indicates that the ISI scores and RMT are different between groups after intervention.

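### ISI and RMT are unranked co-primaries, each tested at P<.05 by a pooled three-arm effect, so the chance of a false primary result is about 8% to 10%, and the test does not isolate HT7 versus r-DLPFC

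*Protocol article*

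**What the plan says.** All references are to the protocol article.

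- **Outcomes.** Section 2.9 lists two primary outcomes without ranking them: "The ISI scores for the severity of CI before and the 10th day of treatment, 30th day of follow-up" and "The RMT for excitability of the motor cortex before and the 10th day of treatment, 30th day of follow-up". No primary visit is named.
- **Threshold.** Section 2.13 sets one rule for every test: a P "value <.05 will be considered as significant".
- **Primary analysis.** Section 2.13.1 states: "We will use univariate repetitive measurement deviation analysis with ISI scores and RMT" at baseline, day 10 and day 30. The result is read as follows: "A significant effect of group indicates that the ISI scores and RMT are different between groups after intervention".
- **Other tests left open.** Section 2.13 also says: "Primary and secondary outcomes according to the measurement times are applicable to univariate repetitive measurement deviation analysis or ANOVA or Kruskal–Wallis test".
- **Arms.** Section 2.5 describes three arms, "namely the experimental group, positive-control group and waiting list control group, 15 cases in each group". Section 2.1 calls the trial positive-controlled and noninferiority, which makes HT7 versus r-DLPFC the main question.
- **Waiting list.** Under section 2.7.3 this arm is untreated for 10 days and then receives the positive-control treatment from day 11.
- **Objectives.** The Introduction (section 1) gives efficacy and mechanism together as the primary objectives. Sections 2.1 and 2.11 call the study a pilot.

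**The concern.** With two equal primaries at 0.05 each, and nothing to say whether one success is enough, a significant RMT result with no ISI benefit could be reported as a positive primary result. The stated 5% then applies to each outcome, not to the primary claim as a whole.

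The second difficulty is what the test measures. A three-arm group effect pooled over visits shows that some arm differs from some other arm on average. It does not say which arms differ or when. The trial is meant to place HT7 stimulation against r-DLPFC stimulation and to inform a later multicentre study, so a primary result that cannot be tied to that comparison is of limited use.

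**Working it through.** **1. Starting point.** The plan states no overall error rate, and the 45 participants in section 2.11 come with no calculation, so there is no figure to reproduce beyond the 0.05 per test. One group test at 0.05 has a 5% false-positive rate (4.9% to 5.3% in simulation).

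**2. Tests in the stated primary analysis.** Section 2.13.1 gives one group effect per outcome, so there are 2 tests. The arms and visits sit inside each test and do not add to the count.

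- If independent: 1 − (1 − 0.05)² = 1 − 0.9025 = 0.0975, or 9.75%.
- Upper bound whatever the correlation: 0.05 + 0.05 = 0.10.

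**3. Allowing for correlation.** The documents give no correlations, so these are assumptions: 0.5 or 0.7 between visits, and 0 to 0.8 between ISI and RMT. The data were simulated with no treatment effect, 15 per arm, three visits and 20,000 runs per setting. The table shows the chance of at least one significant group effect.

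| ISI–RMT correlation | Between-visit 0.5 | Between-visit 0.7 |
|---|---|---|
| 0 | 10.1% | 9.5% |
| 0.3 | 9.8% | 9.8% |
| 0.5 | 9.2% | 9.4% |
| 0.8 | 7.8% | 8.1% |

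The simulation standard error is √(0.0975 × 0.9025 / 20,000) ≈ 0.002, so 10.1% is consistent with 9.75%. Section 2.1 gives 54 participants instead of 45. That discrepancy does not affect these error rates.

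**4. If the by-visit tests are also claimed.** One omnibus test per outcome at each post-baseline visit, which section 2.13 leaves open, gives 2 × 2 = 4 tests. If independent, 1 − 0.95⁴ = 0.185. The simulated range is 13.4% to 17.9%. This applies only if those tests are used as primary claims.

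**5. What the group effect compares.** Three arms give three pairwise differences, and one omnibus effect covers them all. It can be significant because an active arm differs from the waiting list, whether or not HT7 and r-DLPFC differ. A non-significant result would not show noninferiority. The visits also differ in kind:

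| Visit | Waiting-list arm (section 2.7.3) |
|---|---|
| Baseline | Untreated, as are the other arms |
| Day 10 | Still untreated |
| Day 30 | Has received rTMS at r-DLPFC from day 11 |

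An average over these visits mixes a comparison with an untreated arm and a comparison with a treated one.

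**6. After the fix.** A single lead test gives 5%. Testing RMT only after ISI succeeds keeps the overall rate at no more than 5%. Two tests at 0.025 give 1 − 0.975² = 0.0494 if independent (3.9% to 5.1% simulated).

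**The case against.** **Two objectives, two primaries.** The Introduction makes efficacy and mechanism joint primary objectives, so RMT was evidently chosen on purpose, and error control per objective is a defensible convention for separate claims. This stands in part: RMT cannot simply be re-labelled without also aligning the objective. But the plan does not say that the claims are separate. It reads ISI and RMT out in one sentence under one threshold.

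**Both might be required.** That same sentence joins ISI and RMT with an *and*. A rule requiring both would hold the error rate at or below 5%, and at 0.2% to 2.1% in the simulations with no effect on either outcome. The sentence only interprets a result, however, and does not set a rule for success.

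**It is a pilot, and an analysis plan may settle the rest.** Pilot status softens the consequence but not the arithmetic. Details of multiplicity handling and follow-up contrasts may well sit in a document not shown, and their absence is not the point here. The point rests on what is stated: two equal primaries, one threshold, and a pooled omnibus effect as the primary readout.

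**A stronger reading.** A reader might multiply 2 outcomes by 3 pairs of arms and 2 post-baseline visits, count 12 comparisons, and compute 1 − 0.95¹² = 46%. The documents do not support this. No pairwise tests are planned, and section 2.13.1 pools arms and visits into one test per outcome. Independence is also impossible here, because three contrasts among three arms are linearly dependent and both visits measure the same patients.

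**Conclusion.** The point holds in limited form. Following section 2.13.1 as written, the chance of at least one false primary result is about 8% to 10%, or 9.75% if ISI and RMT are independent. The excess over 5% comes from having two unranked primaries, not from the number of arms or visits. It would be larger only if the by-visit tests allowed in section 2.13, or unplanned pairwise tests, were also claimed.

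The figures assume no treatment effect on either outcome, that either outcome alone may be claimed, and the correlations stated above. They concern tests of difference and say nothing about the rate of false noninferiority claims.

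Apart from the error rate, the pooled three-arm effect does not answer HT7 versus r-DLPFC and mixes two visits at which the waiting-list arm has a different treatment status. The plan should be changed on both counts, although the pilot setting limits the harm.

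**What to change.** 1. In sections 2.9 and 2.13.1, name ISI at day 10, HT7 minus r-DLPFC, adjusted for baseline ISI, as the lead primary comparison.
2. Choose one treatment of RMT and state it:
   - make it a key secondary, mechanistic outcome reported as estimates with 95% confidence intervals, and align the primary objective in the Introduction; or
   - keep it primary but test it only after the ISI comparison succeeds, or test each outcome at 0.025 (about 4.9% overall).
3. Report day-30 results as supporting, and note that the waiting-list arm has by then received rTMS.

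The ordered option needs a stated criterion for success on ISI. If that criterion is noninferiority, a margin is required; this is a separate matter.

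The cost is a few sentences, with no new data or participants. RMT alone can no longer carry an unadjusted primary claim, or, with a split alpha, each test has slightly less power. Making RMT secondary also means rewording the stated objective.

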### Secondary outcomes

2.10

Pittsburgh sleep quality index^[26]^ scores for the sleep quality of CI patients, Beck Depression Inventory-2nd edition scores for the depression state, Beck anxiety inventory scores for the anxiety state, and Montreal Cognitive Assessment scores for the cognition state before and the 10th day of treatment. Patients’ diary for tracking their mood, sleep, diet, adverse events, and others during the research. All the dropouts and causes will be documented in case report form.

### Estimation of sample size

2.11

This study is just a pilot study, which designed for efficacy evaluation and mechanism investigation of targeted therapy preliminarily before and after treatment as well as follow-up period. We will plan to enroll a total of 45 participants in this study.

### Randomization

2.12

After recruitment, the patients who meet the eligibility criteria would be randomly and equally divided into 3 groups at a ratio of 1:1:1 with random number table method. Each subject will be registered with a unique ID. After the clinical screening and getting the informed consent forms, subjects will be assigned to experimental group (rTMS at HT7), positive-control group (rTMS at r-DLPFC), and waiting-list control group (no treatment) randomly. Each subject will receive the different stimulation forms, even no stimulating, whereas all subjects will be aware of the grouping.

### Statistical analysis

2.13

Data analysis will be based on intention-to-treat analysis and/or per-protocol analysis principle in the light of data missingness. We will also evaluate the group effect by comparing the analysis results between the above 2 data sets to evaluate robustness of our analytical results.

All data will be analyzed using SPSS23.0 (v23.0; SPSS Inc, Chicago, IL) by 3rd-party statistician. A *P* value <.05 will be considered as significant. Descriptive statistics will be performed with mean, standard deviation, maximum, minimum, and so on by groups and time.

Baseline characteristics of patients will be summarized by groups and compared with Chi-squared for categorical variables, and analysis of variance (ANOVA) (normal distributions) or Kruskal–Wallis test (non-normal distributions) for the continuous variables. Primary and secondary outcomes according to the measurement times are applicable to univariate repetitive measurement deviation analysis or ANOVA or Kruskal–Wallis test. If there is a violation of distribution assumption, appropriate transformation will be used.

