### Study design

2.1

This is a single-center, randomized, positive-controlled, noninferiority clinical pilot trial. A total of 54 participants will be randomized into 3 groups at a ratio of 1:1:1. Participants in the treatment group will be treated with rMS at HT7 acupoint. Participants in the control group will be treated with rTMS at r-DLPFC or waiting treatment.

The whole study period is 35 days, including 5-day baseline observation, 10-day treatment, and 20-days follow-up. Subjects will be evaluated with scales for clinical efficacy before and the 10th day of treatment, 30th day of follow-up, and monitored by rMS/rTMS for therapeutic mechanism before and the 10th day of treatment, 30th day of follow-up (Fig. 1).

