#### Withdrawal criteria

2.3.3

1.Violation of the inclusion criteria and clinical trial protocol or fulfillment of the exclusion criteria;2.Do not receive 10 consecutive treatment days or receipt of <20 rMS sessions;3.Serious adverse events;4.Loss to follow-up;5.Withdrawal of consent by the subject or a legal representative;6.Self-replacement of the treatment package that could affect the study results without permission from the investigator.

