##### rMS at HT7 acupoint

2.7.1.1

The rTMS therapeutic apparatus (CCY-II model; Wuhan YiRuiDe Medical Supplies New Technology Co Ltd, Wuhan, China) were used. rTMS is applied to treat CI according to the modern neuro-rehabilitation theory. Acupoint is only left HT7 (*shenmen*) acupoint according to the TCM theory. After preparation, test the resting motor threshold (RMT): the participants will take the sitting position, keep the mood stable and the muscles relaxed. During stimulating M1 region, the coil will be tangent to the scalp, and it will be advisable to adjust the coil to get the maximum amplitude and the best repeatability of motor evoked potential. The stimulus intensity will begin from 30% and gradually increase at a rate of 2.5%. The minimum stimulus intensity (RMT) will be the abdominal contraction in the abductor pollicis brevis muscles of contralateral thumb in 5 out of 10-times consecutive stimuli; locate the stimulus area: the stimulation coil will be placed at the left HT7 acupoint (on the anteromedical aspect of the wrist, radial to the flexor carpi ulnaris tendon, on the palmar wrist crease) (Fig. 2); set the stimulus parameters: the standard mode is selected as the stimulus mode, for instance the frequency as 1 Hz, the total pulses number as 1800, and the intensity as 25% RMT.^[24]^ Start the stimulation after checking the above parameters, and then remove the coil flap after the stimulation. Participants will be treated 2 sessions per day for 10 consecutive days.

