#### Waiting-list control group

2.7.3

The participants in the waiting group will not be treated within 10 days during the study period, and then treated same as the positive control group from the 11th day.

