### Adverse events observation

2.8

It could be that patients with epilepsy or headache, scalp discomfort, and tinnitus at stimulating are more likely related to rTMS. Regional skin numbness around the HT7 acupoint occur in patients is probably connected to rMS at HT7 acupoint. With the patients’ diary, all adverse events are to be recorded and measured during treatment and the follow-up period. Serious adverse events should be reported to the principal investigator immediately. All details will be documented, coil location and stimulus intensity adjustment (avoid the more sensitive orbitofrontal cortex, 100% RMT → 80% RMT), as well as appropriate medical care will be given at once. For the participants with severe CI during study, they would be administered with Eszopiclone tablets (3 mg Qn). However, if the subjects cannot tolerate the 80% RMT intensity and/or take Eszopiclone tablets more than twice a week, they will be considered as drop outs.

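### The analysis set can be chosen after data collection, and the withdrawal and dropout rules make the intention-to-treat and per-protocol sets likely to differ

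*Protocol article*

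**What the plan says.** All references are to the protocol article.

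- **Analysis set (section 2.13):** "Data analysis will be based on intention-to-treat analysis and/or per-protocol analysis principle in the light of data missingness". The next sentence adds: "We will also evaluate the group effect by comparing the analysis results between the above 2 data sets to evaluate robustness of our analytical results".
- **Withdrawal (section 2.3.3):** the second criterion is "Do not receive 10 consecutive treatment days or receipt of <20 rMS sessions". The first is "Violation of the inclusion criteria and clinical trial protocol or fulfillment of the exclusion criteria". Serious adverse events and unapproved changes of treatment are also listed.
- **Schedule (sections 2.7.1.1 and 2.7.2.1):** for both active arms, "Participants will be treated 2 sessions per day for 10 consecutive days". For the third arm, section 2.7.3 says "The participants in the waiting group will not be treated within 10 days during the study period", with the positive-control treatment starting on day 11.
- **Dropout (section 2.8):** "if the subjects cannot tolerate the 80% RMT intensity and/or take Eszopiclone tablets more than twice a week, they will be considered as drop outs".
- **Design (section 2.1):** "This is a single-center, randomized, positive-controlled, noninferiority clinical pilot trial". Section 2.12 adds that participants know their group.

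**The concern.** An analysis plan should fix who is analysed before anyone sees who is missing. Here the choice between two sets is tied to a feature of the collected data, with no rule and no primary set. This is a stated rule, not a detail left to a statistical analysis plan.

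It would matter little if the two sets were nearly the same. The withdrawal and dropout rules make that unlikely. They remove people for adherence, tolerance and rescue use, all of which arise after randomisation and may differ by arm. A per-protocol comparison is then no longer protected by randomisation. In a noninferiority comparison the choice of set can decide the conclusion, so the usual standard is that both sets agree, not that one is selected.

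**Working it through.** **1. The session threshold against the schedule.** Sections 2.7.1.1 and 2.7.2.1 give 2 sessions a day for 10 days: 2 x 10 = 20. Section 2.3.3 withdraws below 20. The threshold is the whole schedule, so no missed session is tolerated where the rule applies.

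**2. Where the rule applies.**

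- *HT7 arm:* clearly covered, since its treatment is called rMS throughout section 2.7.1.
- *r-DLPFC arm:* unclear. The count names rMS sessions, while this arm's treatment is called rTMS. The usage is loose, because section 2.12 writes rTMS for HT7 as well. The condition on 10 consecutive treatment days can cover this arm, but missing one of two sessions on a day need not breach it.
- *Waiting list:* unclear. This arm has no sessions by day 10 and r-DLPFC treatment afterwards.

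**3. Share withdrawn under the session rule.** The article gives no attendance rate. Assume each session is missed independently with probability q. The share with at least one miss in 20 is 1 - (1 - q)^20.

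| Assumed q | Share withdrawn | Expected left of 15 |
|---|---|---|
| 0.5% | 1 - 0.995^20 = 9.5% | 13.6 |
| 1% | 1 - 0.99^20 = 18.2% | 12.3 |
| 2% | 1 - 0.98^20 = 33.2% | 10.0 |
| 3% | 1 - 0.97^20 = 45.6% | 8.2 |

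The arm size of 15 is from section 2.5 (45 / 3). Section 2.1 gives 54 in total, but the percentages do not depend on this. Misses that cluster in the same people would lower the shares.

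**4. Rules plausibly related to outcome and arm.** Section 2.7 allows Eszopiclone, written as a nightly dose, when symptoms are severe or do not improve. Section 2.8 counts use more than twice a week as dropout. Sustained use as permitted therefore makes the participant a dropout, and the reason for use is poor response. The 80% RMT rule can in practice affect only r-DLPFC stimulation, which is set at 100% RMT (section 2.7.2.1). HT7 stimulation is set at 25% RMT (section 2.7.1.1). The rules can therefore act differently in the two arms of the noninferiority comparison.

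**5. The planned primary analysis.** Section 2.13.1 uses a univariate repeated-measures analysis over baseline, day 10 and day 30. Without imputation, this keeps only people with all three visits. Assume 10% missing at each post-baseline visit:

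- independent between visits: 45 x 0.9 x 0.9 = 36.5;
- the same people miss both visits: 45 x 0.9 = 40.5.

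About 36 to 40 of 45 remain.

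**6. What a free choice of set could cost.** This was simulated with a two-arm, two-sided t-test at 0.05, no true difference, 15 per arm and 40,000 runs. Exclusion rates were the same in both arms. In the outcome-related case, exclusion in one arm had an assumed latent correlation of 0.5 with a worse outcome and was random in the other.

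| Assumed exclusion | Either set usable, random exclusion | Either set usable, outcome-related in one arm | Per-protocol bias in favour of that arm |
|---|---|---|---|
| 10% | 0.064 | 0.073 | 0.10 SD |
| 20% | 0.071 | 0.092 | 0.18 SD |
| 33% | 0.077 | 0.117 | 0.27 SD |

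With the all-randomised set fixed in advance and fully observed, type I error was about 0.049 to 0.050. The other figures describe the case where whichever set is significant may be reported. They mark the upper end of the risk, not what the plan says will happen.

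**The case against.** The strongest defence is that section 2.13 goes on to promise a comparison of the two sets, which suggests that both will be run. The analysis is done by a third-party statistician, section 2.14 describes independent data management, and the trial calls itself a preliminary pilot. The only effect test described in section 2.13.1 is for a difference, so the noninferiority consequence is partly hypothetical.

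This softens the problem but does not remove it. The and/or wording does not guarantee both analyses, neither is primary, and nothing says what follows if they disagree. Pilot status carries limited weight in a trial labelled noninferiority that uses a 0.05 threshold.

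A reader might infer more than the article supports:

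- *Withdrawn participants go unmeasured or leave the intention-to-treat set.* The article says neither. Selection is built into the per-protocol set; for intention-to-treat it depends on follow-up that is not described.
- *The intention-to-treat run must be a complete-case analysis.* That holds only if missing values are not imputed, and imputation may be specified elsewhere.
- *The session rule removes the whole waiting list, or withdraws the same share of both active arms.* The first takes the wording literally and the second loosely. The article supports only that the reach outside the HT7 arm is unclear.
- *The set will be picked on the results.* The stated trigger is missingness. A choice after data collection is possible; a choice on results is not stated.

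**Conclusion.** The point holds in this form. Section 2.13 leaves the analysis set to be settled after data collection, with no primary set and no rule for disagreement. The session rule tolerates no miss in the HT7 arm, which is a fact of the article. The size of its effect is not: about 10% to 46% withdrawn rests on an assumed, independent miss probability of 0.5% to 3% per session. The 36 to 40 of 45 with complete data rests on an assumed 10% missing per post-baseline visit and no imputation. The type I error and bias figures rest on assumed exclusion rates and correlation.

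The dropout rules in section 2.8 make the selection plausibly related to outcome and arm, but the article gives no figure for how strongly. The matter deserves correction before outcome data are examined, because it determines who is analysed for the primary outcomes. If withdrawn participants are in fact not followed, the lost assessments cannot be recovered later.

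**What to change.** **Section 2.13.** Name all randomised participants, analysed as randomised, as the primary set. Make per-protocol a mandatory second analysis, defined before data are seen. Require both to agree for any noninferiority statement. Delete the clause that ties the choice to missingness.

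**Sections 2.3.3 and 2.8.** Separate stopping treatment or deviating from the protocol from leaving follow-up. State that the scheduled day-10 and day-30 assessments are still obtained where the participant consents. Use the session count only to define the per-protocol set, and state which arms it covers.

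**Reconciliation.** Sections 2.3.3, 2.7, 2.7.3 and 2.8 should be made consistent on sessions and rescue use. Which clinical rule is right is for the investigators to settle; no rule is proposed here.

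**Optional.** A likelihood-based mixed model would keep participants who miss one post-baseline visit. It is one way to handle the missing data, not a condition of the fix.

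**Cost.** Wording, plus carrying out visits already scheduled for people who stop treatment.

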#### Secondary outcomes

2.13.2

Continuous outcome variables including Pittsburgh sleep quality index scores, Beck Depression Inventory-2nd edition scores, Beck anxiety inventory scores and Montreal Cognitive Assessment scores before and the 10th day of treatment will be analyzed with ANOVA or Kruskal–Wallis test. Categorical outcome variables in the patients’ diary, Chi-squared test will be used for comparison between groups.

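### Section 2.13 lets an unnamed transformation (and, read literally, a rank test) replace the analysis that 2.13.1 names, so the primary ISI result may not be in ISI points

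*Protocol article*

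**What the plan says.** Section 2.13 of the protocol article covers both outcome classes in one sentence: "Primary and secondary outcomes according to the measurement times are applicable to univariate repetitive measurement deviation analysis or ANOVA", with Kruskal–Wallis as the third choice. The abstract repeats the three-way list. Section 2.13 continues: "If there is a violation of distribution assumption, appropriate transformation will be used". It does not name the transformation, and it does not limit the sentence to one class of outcome.

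Section 2.13.1 is narrower. It states: "We will use univariate repetitive measurement deviation analysis with ISI scores and RMT before and the 10th day of treatment, 30th day of follow-up", and reads the result from the group effect: "A significant effect of group indicates that the ISI scores and RMT are different between groups after intervention". The pre-treatment value is therefore one of the three repeated outcomes. Section 2.13.2 gives the secondary scales a different treatment: they "will be analyzed with ANOVA or Kruskal–Wallis test".

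The only error-rate figure is the threshold in 2.13: a P "value <.05 will be considered as significant". The abstract and section 2.1 label the trial noninferiority, and section 2.5 gives 15 participants per arm.

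**The concern.** The routes that 2.13 opens do not estimate the same thing. The repeated-measures group effect is a mean over visits. A one-way ANOVA compares one visit. Kruskal–Wallis compares ranks and gives no mean difference. A transformed analysis gives a difference on another scale, and here that scale is not named.

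The trial is meant to judge whether stimulation at HT7 is noninferior to stimulation at r-DLPFC. That judgement needs a difference with an interval in units a clinician can set against a tolerable loss, which for ISI means points. If the plan is followed and the distribution assumption is found violated, the primary inference moves off that scale.

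A second worry is that freedom over the method, used after the data are seen, could push the false-positive rate above the stated .05.

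**Working it through.** **1. Can the primary outcomes reach each route?**

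| Route | Section 2.13 | Section 2.13.1 |
|---|---|---|
| Repeated measures, original scale | listed | named |
| Single-visit ANOVA | listed | not mentioned |
| Kruskal–Wallis | listed | not mentioned |
| Transformation | required on violation | not withdrawn |

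So ANOVA and Kruskal–Wallis for ISI and RMT rest on a conflict between two sections. The transformation applies on either reading.

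**2. What a transformation does to the ISI result.** Take log(ISI + 1) as an example; the article names none. A difference of log means back-transforms to a ratio of geometric means of ISI + 1. An illustrative ratio of 0.80 means 0.20 × (8 + 1) = 1.8 points at the lowest eligible score of 8, and 0.20 × (28 + 1) = 5.8 points at the top of the 0–28 scale. One such result does not correspond to one difference in points.

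**3. False-positive rate.** The article derives no error rate or power, so there is no figure to reproduce beyond the .05 threshold. Null trials were simulated with 15 per arm and three visits, scores rounded and limited to 0–28, 10,000 trials per setting (Monte Carlo error about 0.2 to 0.4 points). These inputs are assumptions, not from the article: near-normal scores (means 18, 14, 14; SD 4, 5, 5) or right-skewed scores, and within-patient correlation 0.3, 0.5 or 0.7. The transformation was log(ISI + 1), and the distribution check was Shapiro–Wilk at 0.05.

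| How the test is chosen | Rejections under the null |
|---|---|
| The 2.13.1 test, raw scale, fixed | 4.5–5.3% |
| Any single listed test, fixed | 4.2–5.3% |
| Switched only by the distribution check | 4.8–6.1% |
| Smallest P: repeated measures, raw or log | 5.8–7.1% |
| Smallest P: those two plus day-10 ANOVA (raw or log) and Kruskal–Wallis | 8.9–11.5% |
| Smallest P: also the same three tests at day 30 | 11.5–15.6% |

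A separate run (8,000 trials per setting, correlation 0.5 and 0.7) gave 4.7–5.6% for switching by the check. It gave 7.8–8.8% for the smallest P over repeated measures, day-10 ANOVA and day-10 Kruskal–Wallis.

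**4. Which original-scale model to fix.** Assume both active arms beat the waiting list by δ = 0.8 SD at days 10 and 30. For effects (−δ, −δ, 0) the F-test noncentrality is 15 × (2/3)δ² = 10δ².

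- Day-10 ANOVA: 10 × 0.8² = 6.4, power 58%.
- Day-10 Kruskal–Wallis: 55–56% by simulation.
- Day-10 analysis with baseline as covariate: δ = 0.8/√(1 − ρ²) = 0.92 (ρ = 0.5) or 1.12 (ρ = 0.7); noncentrality 8.5 or 12.5; power 71% or 87%.
- Group effect of 2.13.1, with SD 4, 5, 5: 0.8 × 5 = 4 points at two of three visits averages to (0 + 4 + 4)/3 = 2.67. The SD of a patient's mean is √[(66 + 130ρ)/9] = 3.82 or 4.18, so δ = 0.70 or 0.64; noncentrality 4.9 or 4.1; power 46% or 40%.

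Averaging the pre-treatment visit into the outcome dilutes the effect. Using it as a covariate removes noise instead.

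**The case against.** The strongest reply is that 2.13 is only an umbrella sentence. It ties the method to the measurement times. Section 2.9 gives ISI and RMT three times, section 2.10 gives the secondary scales two, and 2.13.1 and 2.13.2 then assign the methods. In 2.13 the explicit link from non-normality to Kruskal–Wallis is written for baseline characteristics. Much of this stands: a reader might infer that the primary test is free to become a rank test, but the document supports only a conflict to be cleared up. The sorting is also not clean, because the abstract gives the secondary scales three times. And it leaves the transformation sentence untouched.

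A reader might also infer that the plan's false-positive rate exceeds 5%. The document does not support that. Its only trigger is a distribution violation, and following that trigger keeps the rate near 5%. The higher rates require choosing by P value over a menu that includes day-30 single-visit tests the article never spells out.

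It is tempting to blame the rank test for lost power. Against plain ANOVA it costs about 3 points; the larger gain comes from baseline adjustment.

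Nor does this sentence alone prevent a noninferiority judgement. The article states no margin and reads an omnibus group effect, so a raw-scale result would not settle the question either. Descriptive means and SDs by group and time are promised, but they carry no inference.

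Finally, the choice of transformation or normality check may be left to an analysis plan that is not shown, and the trial is a pilot. Their absence is not the point here. The point is that the stated text sends the primary outcomes off their scale and disagrees with itself.

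**Conclusion.** The point holds in a limited form. Sections 2.13 and 2.13.1 must be reconciled. On any reading, the transformation sentence reaches ISI and RMT, so the primary inference may not be in ISI points in a trial labelled noninferiority.

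The error-rate effect is conditional: at most about 6% if a distribution check decides, and about 8% to 16% if the P value decides among repeated-measures and single-visit tests. If only raw or log repeated measures are open, choosing by P gives 5.8–7.1%. All these figures rest on the assumed ISI distributions and correlations.

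The power comparison (71–87% with baseline as covariate, 40–46% for the 2.13.1 group effect) rests on a 0.8 SD benefit of both active arms over the waiting list at both follow-up visits. It does not describe the HT7 versus r-DLPFC contrast. Section 2.7.3 gives the waiting list active treatment from day 11, so a smaller day-30 effect is plausible and would lower the group-effect figure further.

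**What to change.** In 2.13 and the abstract, limit ANOVA, Kruskal–Wallis and the transformation sentence to secondary outcomes.

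In 2.13.1, fix one model for ISI and RMT on the original scale:

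- Day-10 and day-30 values are the outcomes, and the pre-treatment value is a covariate rather than a repeated outcome.
- Report between-group mean differences at each visit, in ISI points (and % output for RMT), with 95% intervals.
- If residuals are clearly non-normal, keep the same estimate and obtain its interval and P value by bootstrap or permutation.
- Label any rank or transformed analysis as sensitivity; it cannot replace the primary result.

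This changes the model that 2.13.1 now describes, because that model yields no baseline-adjusted difference. The cost is a few sentences, a little more analysis work, and the loss of the option to switch tests. No extra data are needed.
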